### Sample Size

The sample size target for this study was 160 (80 in each trial arm). This sample size would provide 0.80 power to detect an effect size of Cohen *d*=0.4 at an alpha of .05.

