### Objectives and Hypotheses

The protocol for the study utilized an RCT to determine whether a 4-month group-based nurse-led intervention delivered over the Web through a mobile phone app when infants were 2-6 months reduced levels of maternal depressive symptoms and improved the quality of maternal caregiving when infants were aged 8-12 months.

We hypothesized that when their infants are aged 12 months, questionnaire scores and direct observation assessments would indicate that mothers who received the app-based intervention would be functioning better than comparison mothers with (1) lower scores on the EPDS [22] assessing the level of maternal depressive symptoms; (2) higher scores on the Parenting Sense of Competence Scale (PSCS) score assessing mothers’ perception of their maternal caregiving competence [23,24] and lower scores on the Parenting Stress Index (PSI) [25] Competence subscale indicating the improved sense of competence in caregiving; and (3) higher scores on the Nursing Child Assessment Satellite Training (NCAST) Parent-Child Interaction Teaching Total Scale scores [26], assessing the quality of mother–child interactions, and lower scores of the PSI Attachment subscale indicating the improved parent-child relationship quality.

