**Figure 1 figure1:**
[figure not shown]
Flow chart of participants. EPDS: Edinburgh Postnatal Depression Scale; N/A: not available.

Following randomization, mothers in the intervention arm were assigned to a group over the Web supported by a CaFHS nurse comprising approximately 20 mothers of similar-aged infants; they were also able to access standard care services as required. The intervention was delivered when infants were aged 2-6 months because this is (1) a key developmental period for infants; (2) a time when mothers are most vulnerable to depressive symptoms; and (3) as previously shown, it is the time when mothers most actively seek information from nurses and want to share and exchange ideas with each other [18].

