### Randomization

The trial used group randomization with blocks of 20 eligible mothers consecutively identified and then randomized to either the intervention or comparison arms of the study. A group randomization sequence was used to determine the arm to which each group was assigned. This approach ensured that mothers’ groups in the intervention arm contained no more than 20 mothers per group. The randomization schedule was generated by a statistician who was independent of the study team. The research team was blind to group allocation at the time of recruitment and assignment of mothers to the study groups. However, due to the nature of the intervention, after the intervention commenced, it was not possible to keep research staff or field workers blind to the groups to which mothers had been allocated. The exception to this was research staff members coding the NCAST Parent-Child Interaction scale, who were blind to the group allocation while completing coding.

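### The stated 0.80 power for d = 0.4 makes no allowance for randomising whole groups of up to 20 mothers; on the conditions checked here it is not reached

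*Protocol article*

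**What the plan says.** The Sample Size section of the protocol article is two sentences long. The first gives the target: "The sample size target for this study was 160 (80 in each trial arm"). The second gives the claim: "This sample size would provide 0.80 power to detect an effect size of Cohen *d*=0.4 at an alpha of .05". It mentions no ICC, design effect, number of groups, sidedness or baseline correlation.

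The Randomization section describes the allocation: "The trial used group randomization with blocks of 20 eligible mothers consecutively identified and then randomized to either the intervention or comparison arms". It adds that "A group randomization sequence was used to determine the arm to which each group was assigned", and that "This approach ensured that mothers’ groups in the intervention arm contained no more than 20 mothers per group". Participants and Recruitment (after Figure 1) says that each intervention group had its own nurse, "comprising approximately 20 mothers of similar-aged infants".

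The Abstract and Participants and Recruitment also speak of randomising mothers, but the Randomization section is the explicit account of the method. The Analysis Plan names general linear modelling with use of baseline data and does not mention groups.

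**The concern.** When whole groups are allocated, the comparison between arms rests on the number of groups as well as the number of mothers. Two things reduce power. Any correlation of outcomes within a group inflates the variance of the arm difference. A test that respects the allocation also takes its degrees of freedom from the number of groups, which costs power even if that correlation is zero. Correlation is plausible here: mothers in an intervention group share a nurse and a chat room, and the curriculum is tailored to each group (Intervention Delivery; Intervention Content).

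This is not detail that an article leaves to a fuller document. The article makes a definite numerical claim that does not fit its own randomisation. The claim matters when results are read: after a non-significant result, a reader who believes the trial had 0.80 power for d = 0.4 would be inclined to conclude that no worthwhile effect exists.

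**Working it through.** **Inputs from the article:** 80 mothers per arm, d = 0.4, alpha .05, stated power 0.80 (Sample Size); groups of at most 20, allocated as groups (Randomization).

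**Inputs not in the article (assumptions):** ICC 0 to 0.05, the same in both arms; number of groups 160/20 = 8, or 4 per arm, which is the minimum for 160 mothers; no dropout; sidedness tried both ways.

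**Step 1: reproduce the stated figure with independent mothers.** SE(d) = √(2/80) = 0.158 and noncentrality = 0.4/0.158 = 2.53, on 158 df.
- Two-sided .05: power 0.71 (detectable d at 0.80 power is 0.446). Not reproduced; the normal approximation needs 99 per arm.
- One-sided .05: power 0.81. Reproduced; 78 per arm are needed.
- Two-sided with baseline adjustment: 0.80 if the baseline-outcome correlation is about 0.43, since 0.4/√(1 − 0.43²) = 0.443. No such correlation is stated.

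The 0.80 is therefore a figure for 160 independent mothers, on a basis that the article does not give.

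**Step 2: allow for 8 groups of 20.** Design effect DE = 1 + (20 − 1) × ICC; SE(d) = √(2 × DE/80); noncentrality = 0.4/SE(d); t test on 8 − 2 = 6 df (critical value 2.447 two-sided, 1.943 one-sided).

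| ICC | DE | SE(d) | Noncentrality | Power, two-sided | Detectable d, two-sided | Power, one-sided | Detectable d, one-sided |
|---|---|---|---|---|---|---|---|
| 0 | 1.00 | 0.158 | 2.53 | 0.56 | 0.53 | 0.72 | 0.45 |
| 0.01 | 1.19 | 0.173 | 2.32 | 0.49 | 0.58 | 0.66 | 0.49 |
| 0.02 | 1.38 | 0.186 | 2.15 | 0.44 | 0.63 | 0.60 | 0.52 |
| 0.05 | 1.95 | 0.221 | 1.81 | 0.33 | 0.74 | 0.48 | 0.62 |

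Detectable d is the effect that gives 0.80 power.

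**Step 3: vary the conditions (power over ICC 0 to 0.05).**
- 10 groups of 16, 8 df: 0.60 to 0.39 two-sided, 0.75 to 0.54 one-sided.
- 12 groups averaging 13.3, 10 df: 0.63 to 0.44 two-sided, 0.76 to 0.58 one-sided.
- 8 groups, two-sided, baseline correlation 0.43: 0.65 to 0.39.
- 8 groups, two-sided, correlation in the intervention arm only, SE(d) = √((DE + 1)/80), Satterthwaite df of 9.9, 8.7 and 6.8: 0.59, 0.54 and 0.43 for ICC 0.01, 0.02 and 0.05.

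None of these reaches 0.80, including those at ICC 0.

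**Step 4: separate the causes.** Two-sided, power is 0.71 before grouping and 0.56 to 0.33 after it. One-sided, it is 0.81 before and 0.72 to 0.48 after. Grouping accounts only for the drop within each pair.

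**The case against.** The strongest reply is that a range such as 0.33 to 0.56 set directly against 0.80 overstates what grouping does. A reader might infer that grouping alone cuts power from 0.80 to one third or one half. The documents do not support that. Sidedness is not stated, the hypotheses are directional ("mothers who received the app-based intervention would be functioning better than comparison mothers"), and the stated figure is reproduced one-sided. If a two-sided test is meant, the calculation already falls short by about 0.09 (0.80 − 0.71) with independent mothers. This part of the objection stands, and the size must be given for both cases.

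The assumptions can also be challenged. No ICC is given. Blocks were formed from consecutive mothers, not from existing communities, and comparison mothers mostly had a single home visit, so correlation in that arm may be small. Eight groups is an inference: blocks were of eligible mothers and written consent came after randomisation, so 160 enrolled mothers may have needed more blocks. All of this stands as a limit on precision. It does not rescue the claim, because 10 or 12 groups, or correlation in one arm only, still leave power below 0.80.

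Baseline adjustment could recover power. At ICC 0 with 8 groups, a two-sided test would need √(1 − r²) = 0.4/0.532 = 0.752, a baseline-outcome correlation of about 0.66. The one-sided equivalent is 0.4/0.446 = 0.897, or about 0.44. The article states no such correlation, so it cannot support the 0.80.

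Finally, recruitment and follow-up are complete, so power cannot be changed, and nothing in the article says that a non-significant result will be read as no effect. Both are true. They limit the remedy to wording and make the risk one of interpretation; the stated figure is still wrong for the described design.

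**Conclusion.** The concern holds in a conditional form. The 0.80 power claim is an individual-level figure that does not match the described group randomisation. With 8 groups of 20, 6 df and an assumed ICC of 0 to 0.05, power for d = 0.4 is about 0.56 to 0.33 two-sided (detectable d 0.53 to 0.74) or 0.72 to 0.48 one-sided (detectable d 0.45 to 0.62).

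The direction does not depend on the ICC, since few randomised units alone keep power below 0.80 at ICC 0. The size does depend on the ICC, the sidedness, the number of groups and any baseline correlation, none of which the article states. No single value should be presented as the trial's true power, and the whole gap from 0.80 should not be put down to grouping.

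**What to change.** - Remove the claim of 0.80 power at d = 0.4.
- State whether the test is one- or two-sided, and how many groups were actually randomised to each arm.
- Restate power and detectable effect for that number of groups over an ICC range such as 0 to 0.05, marked as an assumption, with degrees of freedom from the number of groups. If baseline adjustment is relied on, state the assumed correlation.
- Say that a non-significant result will be interpreted from group-adjusted confidence intervals and not taken as evidence of no effect.

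This changes wording only. No additional enrolment is proposed. The cost is a less favourable stated power and a larger detectable effect. As data analysis has already commenced, the change should be made before results are reported.

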**Methods:**

The trial aimed to recruit and randomize 160 mothers of infants aged 2-8 weeks to either the intervention (eMums plus) or standard care. Assessments were completed when infants were aged 1-2 (preintervention), 8, and 12 months. The primary outcomes were the level of maternal depressive symptoms and the quality of maternal caregiving assessed when infants were aged 12 months. The intervention provided specific support for problems with mood and problems with caregiving. The intervention was delivered by community health nurses as a part of routine service delivery to mothers via a mobile phone app.

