### Analysis Plan

Analyses will be by intention-to-treat and focus on intervention effects on maternal depression (EPDS) [22], mother–child interactions (NCAST) [26], and maternal caregiving competence (PSI and PSCS) [23,25] at 8 and 12 months. General linear modeling techniques will be used when the scores are continuous outcomes, including log-binomial regression for dichotomous outcomes (eg, the percentage of mothers scoring above recommended EPDS cutoff scores). Data collected at baseline will be used to control for any imbalances between the trial arms. Multiple imputations will be used to address missing data where this approach is appropriate.

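### The stated 0.80 power for d = 0.4 with 80 mothers per arm is 0.71 under a two-sided, unadjusted 5% test, and the article declares no basis that would give 0.80

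*Protocol article*

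**What the plan says.** The Sample Size section of the protocol article gives the whole justification in two sentences. The first sets the target: "The sample size target for this study was 160 (80 in each trial arm"). The second gives the power: "This sample size would provide 0.80 power to detect an effect size of Cohen" d of "0.4 at an alpha of .05". Neither sentence states sidedness, the analysis model, a covariate correlation, an allowance for loss, or an ICC.

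Four other places bear on the figure:

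- The Methods part of the abstract shows that 160 is an enrolment number, not an analysed number: "The trial aimed to recruit and randomize 160 mothers".
- Objectives and Hypotheses states a direction, that "mothers who received the app-based intervention would be functioning better than comparison mothers". It does not declare a one-sided test.
- Analysis Plan says "Data collected at baseline will be used to control for any imbalances between the trial arms", without a baseline-outcome correlation or a link to the power figure. On missing data it says "Multiple imputations will be used to address missing data where this approach is appropriate".
- Randomization describes allocating whole groups of 20 consecutively identified mothers to an arm.

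**The concern.** An alpha of .05 given without qualification is normally read as two-sided. On that reading the four printed inputs (80 per arm, d = 0.4, alpha .05, power 0.80) do not fit together: the power is about nine percentage points lower than stated.

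This is the article's only justification of the trial's size. A reader who takes 0.80 at face value would put the chance of missing a true effect of d = 0.4 at 20%. On the two-sided reading it is about 29%, before any allowance for clustering or loss. Recruitment and follow-up are complete, so the consequence is mainly for interpretation: a non-significant result would look like stronger evidence against an effect of the planned size than it is.

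**Working it through.** **Inputs from the Sample Size section.** n = 80 per arm, d = 0.4, alpha = .05, stated power 0.80. Sidedness and model are not given, so each plausible reading is tried.

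**Formula.** For a two-sample t test with n per arm, the noncentrality is d × √(n/2) = 0.4 × √40 = 2.530, with 2 × 80 − 2 = 158 degrees of freedom. Power is the probability that a noncentral t variable with these parameters passes the critical value.

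**1. Reproducing the stated 0.80.** With a one-sided 5% test the critical value is 1.655 and the power is 0.809. The normal approximation gives Φ(2.530 − 1.645) = 0.812. The number needed for 0.80 is 78 per arm, against 80 stated. So a one-sided 5% test does reproduce the printed figure.

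**2. Two-sided 5% test.** The critical value is 1.975 and the power is 0.710. The normal approximation gives Φ(2.530 − 1.960) = 0.716. The chance of missing d = 0.4 is 1 − 0.71 = 0.29.

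**3. What 0.80 would need, two-sided.** By the normal approximation, n = 2 × [(1.960 + 0.842)/0.4]² = 98.1, so 99 per arm. By the noncentral t it is 99.1, so 100 per arm, or 200 in total against 160. Holding n at 80, the detectable effect is 0.443 (normal) or 0.446 (t), that is, d of about 0.45.

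**4. Two-sided with baseline adjustment.** A covariate with baseline-outcome correlation r reduces the residual SD by √(1 − r²), which is like having n/(1 − r²) mothers per arm. Setting 80/(1 − r²) = 99.1 gives r = √(1 − 80/99.1) = 0.44; rounding the requirement up to 100 gives r = √0.20 = 0.45. The normal approximation gives 0.43. At r = 0.3 the power is 0.76 and at r = 0.5 it is 0.83 (normal approximation). So this route also reaches 0.80, but it rests on a correlation that the article does not give.

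**5. Features that lower the figure.** The loss rates and ICCs below are assumptions; the documents give neither. All figures are for d = 0.4, alpha .05, unadjusted, by the noncentral t.

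| Assumption | Effective n per arm | Two-sided power | One-sided power |
|---|---|---|---|
| Independent mothers, no loss | 80 | 0.71 | 0.81 |
| 10% loss, no clustering | 72 | 0.66 | 0.77 |
| 15% loss, no clustering | 68 | 0.64 | 0.75 |
| 20% loss, no clustering | 64 | 0.61 | 0.73 |
| ICC 0.01, groups of 20, no loss | 80/1.19 = 67.2 | 0.63 | 0.75 |
| ICC 0.05, groups of 20, no loss | 80/1.95 = 41.0 | 0.43 | 0.56 |

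The design effect is 1 + (20 − 1) × ICC. It is a simple inflation and ignores the small number of groups: 160/20 = 8, about four per arm. A test that took its degrees of freedom from the groups would have less power again.

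**The case against.** The strongest reply is that the article never says the test is two-sided. Its hypotheses are all directional, and a one-sided 5% test gives 0.81, close to the printed value. The Analysis Plan also intends general linear models with baseline data, and the outcome measures were taken before the intervention, so a gain from baseline adjustment is a realistic alternative basis. A condensed article may leave sidedness, model and loss allowance to a fuller document that is not shown.

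Much of this stands. A reader might infer that 0.80 is simply an arithmetic error, or that only a one-sided test could produce it. The documents support neither inference: sidedness is unstated, and two separate routes reach the figure. Nor do they show that the authors used a one-sided test. The missing loss allowance is not counted here as a separate error.

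What does not stand is that either route is declared. A predicted direction is not a one-sided test, and baseline data are described as a control for imbalance, not as the source of the power. The article prints a definite power with an unqualified alpha, and under the usual reading that number does not follow from its own inputs. Even on the one-sided reading there is almost no margin: 78 of the 80 mothers in each arm would have to be analysed to keep 0.80.

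**Conclusion.** The concern holds in a limited form. Under a two-sided, unadjusted 5% comparison of 80 independent mothers per arm with no loss, power for d = 0.4 is 0.71, not 0.80. Reaching 0.80 needs about 100 per arm, or d = 0.45 at the stated size. The printed 0.80 requires either a one-sided 5% test or a baseline-outcome correlation of about 0.44 to 0.45, and the article gives neither as its basis.

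The 0.71 depends only on the article's own inputs and the two-sided convention. It is an upper figure for the unadjusted analysis, since a positive ICC within the randomised groups and any loss both reduce it. How far they reduce it depends on values that the article does not report, so the clustered and reduced-sample figures are illustrations, not estimates for this trial.

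This should be fixed, but it does not call the data or the design into question. With follow-up complete, its importance lies in how a null result is read.

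**What to change.** Restate the power sentence in the Sample Size section with the sidedness and model named. For example: with 80 mothers per arm, a two-sided 5% test has power 0.71 for d = 0.4, or 0.80 for d = 0.45, assuming independent mothers, no loss and no covariate adjustment.

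If the original 0.80 relied on baseline adjustment, say so and give the assumed correlation and its source. If it relied on a one-sided test, say that this was the basis and give the two-sided figure beside it.

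Add one sentence saying that the unadjusted figure is an upper bound, because groups of 20 were randomised and not every randomised mother will be analysed. Give the power under a stated ICC and a stated loss, with both labelled as assumptions where they are assumed.

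The cost is two or three sentences and a less favourable stated power. No extra mothers and no change to the design or data are needed.

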### Ethics

Ethics approval was received from the Women’s and Children’s Health Network Human Research Ethics Committee (approval numbers SSA/16/WCHN/016, HREC/16/WCHN/014).

## Results

Participant recruitment was carried out from March to July 2017. Follow-up data collection was completed in June 2018. Data analysis has commenced.

## Discussion

The broad aim of this study was to assess whether a 4-month group-based, nurse-led intervention delivered through a mobile phone app when infants were aged 2-6 months reduced levels of maternal depressive symptoms and improved the quality of maternal caregiving when infants were aged 8-12 months. The intervention was assessed in a pragmatic RCT with the intervention delivered as part of the routine service practice by community child health nurses. The advantage of this methodology is that when an intervention is found to improve child and maternal outcomes services, it can be more readily taken up and continue providing this service using staff already experienced in delivering the intervention. It has been widely recognized in the medical and public health literature that results from such trials are more likely to be translated into practice than results from trials conducted in academic or research settings [27,28].

A large number of mothers experience subthreshold levels of postnatal depression, and it has been recognized that even subthreshold levels of depression can adversely affect maternal functioning and infant development. If the results from the trial demonstrate a positive effect, it will have established the basis for a new app-based approach that can help a large number of mothers experiencing depressive symptoms and caregiving difficulties early in their infant’s life, including mothers in rural communities who frequently have limited access to clinic-based services.

## Abbreviations

CaFHS: Child and Family Health Service
EPDS: Edinburgh Postnatal Depression Scale
NCAST: Nursing Child Assessment Satellite Training
PSCS: Parenting Sense of Competence Scale
PSI: Parenting Stress Index
RCT: randomized controlled trial
